### Study population

Patients at least 20 years of age who have moderate or severe intermittent claudication or critical limb ischemia (Rutherford score of 2 to 6, except any patient who has undergone or plans to take major amputation) will be screened for study enrollment. A patient will be enrolled if they meet all of the inclusion and have none of the exclusion criteria. Inclusion criteria consist of clinical and anatomical criteria. The clinical criteria includes symptomatic peripheral-artery disease with moderate to severe claudication (Rutherford score of 2 to 3), chronic critical limb ischemia with resting ischemic pain (Rutherford score of 4), or chronic critical limb ischemia with ischemic ulcers (Rutherford score of 5 to 6), and patient must provide written informed consent. The anatomical criteria includes stenosis of more than 50% of, or occlusion of the ipsilateral femoropopliteal artery, patent (≤50% stenosis) ipsilateral iliac artery, or concomitantly treatable ipsilateral iliac lesions (≤30% residual stenosis), and at least one patent (less than 50% stenosis) tibioperoneal run-off vessel. Patients meeting any of the following criteria will be excluded from the study: failure to provide written informed consent; a history of major bleeding within prior two months; known hypersensitivity or contraindication to any of the following medications: heparin, aspirin, clopidogrel, cilostazol, or contrast agent; acute limb ischemia; previous bypass surgery or stenting of the ipsilateral femoropopliteal artery; untreated inflow disease of the ipsilateral pelvic arteries (>50% stenosis or occlusion); patients who have undergone major amputation (amputation of above the ankle) or major amputation is planned or required; patients with a life expectancy of less than one year due to comorbidities.

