## Appendix

### Endpoints definitions

Binary restenosis: defined as a reduction in the luminal diameter of >50% according to the worst angiographic view at the narrowest site within the treated segment plus the 10-mm segments proximal and distal to the treated segment by catheter angiography or PSVR ≥2.5 (PSVR = peak systolic velocity within the area of stenosis divided by peak systolic velocity in a normal adjacent proximal artery segment) or total occlusion by duplex ultrasound. Stent fracture rate according fracture grade (minor, moderate, severe) [12]: plain X-ray examinations for the stent fracture are used or performed using at least two different angulations (30 to 45° difference) and the highest available magnification. Stent fracture is classified as minor (single strut fracture), moderate (fracture of more than 2 struts), or severe (complete separation of stent segments). Target lesion revascularization (TLR): defined as any repeat percutaneous intervention of the target lesion or bypass surgery of the target vessel performed for restenosis because of a return of ischemic symptoms, decrease of at least 1 Rutherford category, decrease in the ankle brachial index of >0.15, or restenosis of >50% as measured by catheter angiography. The target lesion is defined as the treated segment from 10 mm proximal to the stent and to 10 mm distal to the stent. Target extremity revascularization (TER): defined as any repeat percutaneous intervention of the target extremity or bypass surgery of the target extremity performed for restenosis because of a return of ischemic symptoms, decrease of at least 1 Rutherford category, decrease in the ankle brachial index of >0.15, or restenosis of >50% as measured by catheter angiography. Limb salvage: defined as survival free of amputation. Amputation is defined as above-ankle amputation of the index limb. Sustained clinical improvement rate [36, 37]: defined as persistent ABI value ≥0.15 and persistent improvement of ≥1 class according to Rutherford throughout follow-up when compared with baseline without the need for repeat TLR in surviving patients. Late loss: defined as a change in MLD from final angiogram to follow-up. Major adverse cardiac events (MACE): defined as composite of all-cause death, myocardial infarction, cerebrovascular stroke, and target lesion revascularization.

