### Immediate outcomes

Acute lesion success: defined as a residual stenosis of ≤30% without flow-limiting dissection in the worst angiographic view. Definition of suboptimal result: residual pressure gradient of >10 mmHg, residual stenosis of >30%, or flow-limiting dissection. Acute hemodynamic success: defined as a ≥ 0.15 improvement in the ankle-brachial index from pre-procedure to immediately post-procedure (discharge). Clinical success: defined as an improvement of baseline symptoms by at least 1 Rutherford category that was sustained throughout follow-up with no additional intervention.

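### Sustained clinical improvement sets its ankle-brachial index (ABI) criterion as a level of 0.15 instead of a change, and counts survivors only

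*Protocol article*

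**What the plan says.** The Outcome measures section lists sustained clinical improvement at 12 months as secondary endpoint 4, TLR as endpoint 5 and TER as endpoint 6. The Appendix (Endpoints definitions) gives the rules.

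- **Sustained clinical improvement:** "defined as persistent ABI value ≥0.15 and persistent improvement of ≥1 class according to Rutherford throughout follow-up when compared with baseline", and "without the need for repeat TLR in surviving patients".
- **TLR:** "defined as any repeat percutaneous intervention of the target lesion or bypass surgery of the target vessel performed for restenosis", where the restenosis is treated "because of a return of ischemic symptoms, decrease of at least 1 Rutherford category, decrease in the ankle brachial index of >0.15, or restenosis of" more than 50% on catheter angiography. TER uses the same list of reasons for the whole extremity.
- **Acute hemodynamic success** (Appendix, Immediate outcomes): "defined as a ≥ 0.15 improvement in the ankle-brachial index from pre-procedure to immediately post-procedure".

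The Study population section fixes the direction of the Rutherford scale. Scores of 2 to 3 are claudication, and the top of the scale is "chronic critical limb ischemia with ischemic ulcers (Rutherford score of 5 to 6". The Statistical analysis section says that primary and secondary endpoints will be analyzed by intention to treat, meaning every subject assigned to a group, and also per protocol.

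**The concern.** Three parts of these definitions do not fit the rest of the article.

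1. The ABI component of endpoint 4 is worded as a value to be reached. If it is programmed that way, the hemodynamic part of a combined clinical and hemodynamic endpoint does almost no work.
2. Endpoint 4 is limited to survivors. Survival is known only after randomization, so the denominator is not the intention-to-treat set, and a patient who dies leaves the denominator instead of counting as a failure.
3. TLR and TER name a Rutherford decrease as a sign of deterioration, although a lower category is better.

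The first matters most. A patient whose symptoms improve but whose ABI does not rise is a success under the literal rule and a failure under the rule that the article uses elsewhere.

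**Working it through.** **Sample size, to see whether it is touched.** Inputs from the Sample size calculation section: patency 65% and 80%, 5% significance (two-sided assumed), 80% power, 1:1, 20% dropout. With mean proportion 0.725:

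n = [1.96 × √(2 × 0.725 × 0.275) + 0.8416 × √(0.65 × 0.35 + 0.80 × 0.20)]² / 0.15²
= (1.238 + 0.524)² / 0.0225 ≈ 137.9, so 138 per group.

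138 / 0.80 = 172.5, so 173 per group and 346 in total. This matches the article. The calculation rests on restenosis alone, so the point below does not alter it.

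**How 0.15 is used.**

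| Place | Use of 0.15 |
|---|---|
| Acute hemodynamic success | rise in ABI |
| TLR and TER | fall in ABI |
| Sustained clinical improvement | ABI value |

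Only the last is a level.

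**What a level of 0.15 means.** The Appendix computes ABI as ankle pressure over the highest brachial pressure, so ankle pressure = ABI × brachial pressure. The article gives no brachial pressures; 120 to 160 mmHg is assumed.

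- 0.15 × 120 = 18 mmHg
- 0.15 × 140 = 21 mmHg
- 0.15 × 160 = 24 mmHg

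**Level against change.** The article gives no baseline ABI; 0.4 to 0.8 is assumed. The largest passing fall is baseline − 0.15. The change rule needs baseline + 0.15.

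| Baseline ABI | Largest fall that still passes as a level | Follow-up ABI needed for a rise of 0.15 |
|---|---|---|
| 0.4 | 0.25 | 0.55 |
| 0.6 | 0.45 | 0.75 |
| 0.8 | 0.65 | 0.95 |

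Under the literal rule a limb may lose 0.25 to 0.65 and still pass on ABI. What then decides the endpoint is Rutherford improvement without TLR. That is close to the separate Clinical success definition under Immediate outcomes, which asks for a sustained Rutherford gain with no further intervention.

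**Survivors.** If a share m of an arm dies, and the success rate among survivors is p, the rate in all assigned patients with death as failure is p × (1 − m). The article gives no expected mortality; 2%, 5% and 10% are assumed, equal in both arms, with other losses ignored.

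| m | Deaths per arm of 173 | A 10-point difference among survivors becomes |
|---|---|---|
| 2% | 3.5 | 9.8 points |
| 5% | 8.7 | 9.5 points |
| 10% | 17.3 | 9.0 points |

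With equal mortality the rates shrink slightly and the comparison keeps its direction. Only unequal mortality would distort it, and nothing in the article suggests that.

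**Rutherford direction.** A move from 3 to 2 is a decrease and an improvement; a move from 3 to 4 is an increase and a worsening. The TLR and TER wording therefore names the wrong direction. Both definitions nevertheless require a repeat intervention or bypass carried out for restenosis, and the four reasons are alternatives.

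**The case against.** The strongest reply is that no careful reader would apply 0.15 as a level. The closing reference to baseline in "defined as persistent ABI value ≥0.15 and persistent improvement of ≥1 class according to Rutherford throughout follow-up when compared with baseline" can govern the ABI as well as the Rutherford class, and every other 0.15 in the article is a change. The definition also cites two published sources that are not at hand. On this view a word was left out, and the 18 to 24 mmHg figure measures only a misreading. This stands as to intent: an increase was probably meant. It does not remove the defect, because the text says value, and a programmer or adjudicator who follows the text applies a different rule.

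A reader might infer that endpoint 4 needs nothing more than an ABI of 0.15. The article does not support that. Rutherford improvement and freedom from TLR are joined to the ABI criterion, so a patient who does not improve clinically, or who has TLR, still fails.

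A reader might also infer that TLR and TER will count improved patients and miss worsened ones. That is not shown. An improved patient with no reintervention for restenosis is never an event. A worsened patient who has one would ordinarily qualify through returning symptoms, a fall in ABI or restenosis above 50%. In a list of reasons to reintervene, decrease most naturally means deterioration.

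On survivors, the restriction is explicit, and deaths are not hidden: all-cause death is part of the major adverse event composite, and death is also analyzed by Kaplan-Meier. Counting death as failure is one defensible choice among several. The conflict with the stated analysis set remains, and the same Appendix defines limb salvage as amputation-free survival, which does count death against the patient.

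**Conclusion.** The concern holds for the definition of secondary endpoint 4. Its ABI component is written as a level where the article otherwise uses a change, and as written it excludes almost no patient. This rests on the assumed brachial pressures of 120 to 160 mmHg and baseline ABIs of 0.4 to 0.8, but any plausible values give the same conclusion. How many patients the two readings would classify differently cannot be computed from the article.

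The survivor restriction contradicts the stated intention-to-treat set. Its numerical effect is small if mortality is similar in both arms, and a bias between stents is not demonstrated.

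The Rutherford wording in TLR and TER runs against the scale. It is a wording correction with probably little effect on classification. TLR also enters endpoint 4 and the Appendix definition of major adverse events, but that adds nothing unless TLR classification itself changes.

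The primary endpoint, its test and the 346 patients are unaffected. Severity is minor to moderate.

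**What to change.** 1. State the ABI component of sustained clinical improvement as a persistent increase of at least 0.15 compared with the pre-procedure value. Keep the Rutherford and no-TLR conditions as they are.
2. Report the endpoint in all assigned patients with death counted as not sustained, at least alongside the survivor version, and say which of the two is the main analysis.
3. In the TLR and TER definitions, replace the Rutherford decrease with worsening, that is, an increase of one category or more.

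The cost is three wording changes and one extra tabulation. The components are already defined in the article, and no patients need to be added. Recruitment is described as ongoing, so the changes can be made before analysis. If the ABI criterion was always going to be applied as a change, the first edit alters no result; if it was going to be applied as a level, the reported rate will fall. The all-assigned rate will be lower than the survivor rate whenever there are deaths.

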### Immediate outcomes

Acute lesion success: defined as a residual stenosis of ≤30% without flow-limiting dissection in the worst angiographic view. Definition of suboptimal result: residual pressure gradient of >10 mmHg, residual stenosis of >30%, or flow-limiting dissection. Acute hemodynamic success: defined as a ≥ 0.15 improvement in the ankle-brachial index from pre-procedure to immediately post-procedure (discharge). Clinical success: defined as an improvement of baseline symptoms by at least 1 Rutherford category that was sustained throughout follow-up with no additional intervention.

### QCA (Qualitative Comparative Analysis) data definition and variables

Reference vessel diameter (obtained from averaging 5-mm segments proximal and distal to the lesion), minimal luminal diameter (MLD), acute gain (change in MLD from baseline to post-intervention), late loss (change in MLD from the final angiogram to follow-up), percent diameter stenosis, total reocclusion rate, and binary (>50%) restenosis rate [38].

### Ankle-brachial index (ABI) calculation

Measurement of highest systolic pressure in both arms, measurement of systolic pressure in both legs, use highest ankle pressure (dorsalis pedis or posterior tibialis) for each leg, and calculate ratio of each ankle to brachial pressure by dividing each ankle by highest brachial pressure.

### Bleeding and hemorrhagic complications

An episode of bleeding is defined by the TIMI (Thrombolysis In Myocardial Infarction) criteria [39] as:

Major: overt clinical bleeding (or documented intracranial or retroperitoneal hemorrhage) associated with a drop in hemoglobin (Hgb) of greater than 5 g/dl (0.5 g/l) or in hematocrit (Hct) of greater than 15% (absolute). A patient who experiences an intracranial hemorrhage should be considered to have a major hemorrhage. Minor: overt clinical bleeding associated with a fall in hemoglobin of 3 to less than or equal to 5 g/dl (0.5 g/l) or in hematocrit of 9% to less than or equal to 15% (absolute). None: no bleeding event that meets the major or minor definition. In calculating the fall in hemoglobin or hematocrit, a transfusion of whole blood or packed red blood cells is counted as 1 g/dl (0.1 g/l) hemoglobin or 3% absolute in hematocrit. This would be in addition to the actual fall in hemoglobin or hematocrit. To account for transfusion, hemoglobin and hematocrit measurements will be adjusted for any packed red blood cells or whole blood given between baseline and post-transfusion measurements. A transfusion of one unit of blood will be assumed to result in an increase of 1 g/dL in Hgb or of 3% in Hct. Thus, to calculate the true change in Hgb or Hct if there has been an intervening transfusion between two blood measurements, the following calculations should be performed:

The following will be classified as ‘instrumented’ major bleeding that is considered to be associated with the catheterization laboratory visit: major percutaneous entry site: bleeding occurred at the percutaneous entry site during or after the catheterization laboratory visit until discharge. The bleeding should require a transfusion and/or prolong the health care facility stay, and/or cause a drop in Hgb >5 g/dL. Bleeding at the percutaneous entry site can be external or a hematoma >10 cm for femoral access or >2 cm for radial access or >5 cm for brachial access. major retroperitoneal, gastrointestinal, genital, and urinary: bleeding occurred during or after the catheterization laboratory visit until discharge. The bleeding either requires surgical intervention (for example, to relieve nerve compression), and/or requires a transfusion and/or prolongs the health care facility stay, and/or causes a drop in hemoglobin > 5.0 g/dL. major other or unknown: bleeding occurred at other or unknown locations during or after the catheterization laboratory visit until discharge. The bleeding should require a transfusion and/or prolong the healthcare facility stay and/or cause a drop in Hgb > 5 g/dL.

## Abbreviations

CTO: Chronic total occlusion
ECS: European Society of Cardiology
U.S. FDA: United State Food and Drug Administration
PAD: Peripheral arterial disease
PCI: Percutaneous coronary intervention
PSVR: Peak systolic velocity ratio
SFA: superficial femoral artery
TASC: Transatlantic Inter-Society Consensus.
